## Exclusion Criteria

1. Subject has had prior or current PCa therapies, such as biologic, chemotherapy, hormone therapy, radiotherapy or surgery for PCa. Subjects may not have had undergone pelvic radiation, chemotherapy or immunotherapy treatment for a separate hematologic or visceral malignancy within 6-months of enrollment in the present study.
2. Subjects with locally advanced, nodal or metastatic prostate cancer.
3. Subjects who are unfit for pelvic mpMRI scanning (e.g., severe claustrophobia), permanent cardiac pacemaker, metallic implants that are likely to contribute to significant image artifacts, allergy or contraindication to gadolinium contrast agent.
4. History of allergy or intolerance to study drug components.
5. History of bilateral orchiectomy.
6. If the subject has an uncontrolled or major debilitating inter-current illness.
7. Subjects who are receiving any other investigational agents, or who have received other investigational agents in the past and who are no longer receiving these investigational agents may be eligible at the discretion of the principal investigator (PI).
8. Judgment by the treating investigator or PI that the subject is unsuitable to participate in the study and the subject is unlikely to comply with study procedures, restrictions, and requirements.

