**The following principles will dictate the ablation template**:

The treatment or ablation zone will cover the area of the gland in which the CSPCa lesion(s) (GG ≥2) have been identified by the subject's MRI-TB study as follows:

1. A maximum of 60-75% prostate ablation to include all CSPCa. If the patient has more than one focal lesion on one side, all CSPCa lesions will be destroyed.
2. Treatment may reach the urethra and may cross the midline anteriorly or posteriorly.
3. At least one neurovascular bundle must be avoided by ensuring a minimum distance of ablation zone border to the contralateral neurovascular bundle of 5 mm. If ablation of CSPCa cannot be done without damaging both neurovascular bundles, the patient will not be considered for FT.
4. Up to one redo FT treatment is permissible; if either the protocol’s 6-month MRI-TB result(s) of ablated/treated prostate tissue, or a ‘for-cause’ prostate biopsy (see [section 8.7](#_For_Cause_Tests)) are positive at any point in follow-up.

**The following diagrams illustrate some possible interventions using focal therapy: In each of these scenarios below contralateral nerves were spared.**

[figure not shown]

[figure not shown]

[figure not shown]

[figure not shown]

[figure not shown]

[figure not shown]

[figure not shown]

[figure not shown]

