## Post-Focal Therapy Treatment Efficacy/Surveillance mpMRI and MRI-TB

At 12-months from the time of FT, a SOC mpMRI and MRI-TB will be performed to determine treatment response. Both the imaging study and prostate biopsy results will be used to measure efficacy of the proposed combination treatment. However, if a patient has any other post-treatment biopsy results these may also be used to assess for post-treatment efficacy even if not performed with an mpMRI guided biopsy.

Specifically, an MRI-TB will sample the ablated and unablated prostate tissue to determine if residual CSPCa (GG ≥2) remains in the treated and/or untreated prostate tissue. The mpMRI used for the MRI-TB will follow the same imaging protocol as the pre-treatment study and reported in the same manner. Documentation of the biopsy site(s) will be required. If a new suspicious radiographic lesion(s) is/are detected on the subject’s 12-month mpMRI which was/were not present in the pre-treatment [screening] mpMRI then the targeted biopsy cores of the suspicious area(s) will be obtained. Otherwise, if no suspicious lesions are noted in the 12-month mpMRI then random biopsies from the unablated prostate tissue will be obtained per SOC during the MRI-TB.

- Two 18-gauge biopsy cores will be collected from the ablated area(s) and one each from periablation zone and untreated prostate for biobanking and exploratory outcomes on correlatives.

If the 12-month MRI-TB identifies the presence of CSPCa in the ablated or unablated prostate tissue then the patient will be offered a second treatment with FT (if eligible for such treatments) and the follow-up visits for the re-treatment will be the same as the primary treatment. The patients will stay in the study and will continue to be followed up until 12-months from the first FT procedure. For patients with residual/recurrent cancer who decline or are ineligible for a second FT procedure, one of the whole gland treatments, either radical prostatectomy, whole gland ablation or radiation therapy, will be offered. These data will be recorded as part of report of secondary outcomes. Patients who choose to undergo whole gland treatment during the study follow-up will exit the study at this point. HRQOL surveys, PSA and testosterone levels will be obtained at the exit.

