## For Cause Tests

Clinicians can biopsy the prostate following primary FT if there is a clinically significant rise in PSA (≥2 ng/mL higher from the subject’s post-FT PSA nadir, i.e., ‘for cause’ prostate biopsy) or clinical suspicion for progression of PCa. Nadir value will be defined as the lowest PSA value obtained after completion of combination treatment and recovery to non-castrate levels of testosterone (defined as testosterone levels >50 ng/mL). If there is a concern of prostate inflammation/infection due to a recent biopsy or urinary tract infection, patients will be treated with a course of antibiotics before repeating PSA. If the confirmatory PSA again demonstrates rise of 2 ng/mL above nadir, the patient will be evaluated further for local disease recurrence/progression. A mpMRI will be required prior to the biopsy unless the patient has developed a contraindication to biopsy.

If the untreated area is biopsied, the specimens will be individually identified according to location as determined by a standard protocol.

The specimen will be processed according to standard protocol and examined by a pathologist to note the following features for each core taken.

- Presence of adenocarcinoma
- Grade group
- Length of cancer and total core length

Additional Tests: ‘for cause’ additional tests such as ultrasound, CTAP, BS or PSMA/PET scan will be permissible as SOC practice.

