## Trial Monitoring

This study will be remotely monitored by the University of Chicago CTSO Quality Unit Monitoring Staff in accordance with the standard operating procedure titled Monitoring of Multi-Institutional Investigator Initiated Clinical Trials.

Prior to subject recruitment, research staff will undergo a Site Initiation Teleconference to be conducted by the designated University of Chicago research team. The site’s Study Lead Principal Investigator and their study staff must attend the site initiation meeting.

Monitoring will be conducted to verify the following:

- - - - Adherence to the protocol
      - Completeness and accuracy of study data and samples collected
      - Compliance with regulations
      - Submission of required source documents

Research staff will also undergo a site close-out teleconference upon completion, termination or cancellation of a study to ensure fulfillment of study obligations during the conduct of the study, and to ensure that the Principal Investigator is aware of his/her ongoing responsibilities.

Protocol deviations are to be documented using the Protocol Deviation Form and sent via email to [[contact]](mailto:[contact]). Deviations that are considered major because they impact subject safety or alter the risk/benefit ratio, compromise the integrity of the study data, and/or affect subjects’ willingness to participate in the study must be reported within 7 days. Please contact the University of Chicago CRA ([[contact]](mailto:[contact])) if you have questions about how to report deviations. All major protocol deviations should also be reported to the local IRB of record according to their policies and procedures.

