# APPENDIX B Prostate Multiparametric Magnetic Resonance Imaging and Transperineal or Transrectal Magnetic Resonance Imaging Targeted Prostate Biopsy Protocols

The mpMRI protocol: see Prostate Imaging Reporting and Data system version 2.1 ([PI-RADS version 2.1](https://www.acr.org/-/media/ACR/Files/RADS/Pi-RADS/PIRADS-V2-1.pdf?la=en))

Pre-operative and all post-FT imaging will be performed using either a 1.5 or 3 Tesla scanner and a pelvic phased array receiver, with or without an endorectal coil. A full protocol of T1 and T2 weighted turbo-spin echo images and a dynamic post gadolinium volume acquisition will be used for both pre-operative diagnostic and planning scans and post-operative assessment of ablation. The protocol will be standardized as below:

- T1 weighted axial of pelvis: to detect lymphadenopathy and other pelvic
- pathologies
- T2 axial small field of view prostate: cancer detection and volume estimation
- T2 small field of view coronal: for cancer detection and to accurately determine the position of prostatic apex and external sphincter
- T1 axial small field of view: to detect hemorrhage
- Dynamic contrast-enhanced: for tumor enhancement.
- Post contrast small field of view fat saturated T1 axis: high-resolution images of enhancement
- Diffusion weighted axial scans of prostate: to detect restricted diffusion in tumor

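### The waiver of mpMRI before a for-cause biopsy is tied to the wrong procedure, so a man who can no longer have the scan has no exemption

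*Protocol*

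**What the plan says.** The For Cause Tests section lets clinicians biopsy the prostate after focal therapy (FT) for a PSA rise of at least 2 ng/mL above the post-FT nadir, or for clinical suspicion of progression. Where a repeat PSA confirms the rise, "the patient will be evaluated further for local disease recurrence/progression". The next sentence sets the imaging rule and its only exception: "A mpMRI will be required prior to the biopsy unless the patient has developed a contraindication to biopsy".

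Five other places bear on the point:

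- **Appendix B, scope.** "Pre-operative and all post-FT imaging will be performed using either a 1.5 or 3 Tesla scanner".
- **Appendix B, sequences.** The protocol includes contrast: "a dynamic post gadolinium volume acquisition will be used for both pre-operative diagnostic and planning scans and post-operative assessment of ablation". No non-contrast alternative is given.
- **Exclusion Criteria (5.2), criterion 3.** Men unfit for pelvic MRI are excluded at entry. The listed conditions include "permanent cardiac pacemaker, metallic implants that are likely to contribute to significant image artifacts, allergy or contraindication to gadolinium contrast agent".
- **Post-Focal Therapy Treatment Efficacy/Surveillance mpMRI and MRI-TB.** Of other post-treatment biopsy results it says that "these may also be used to assess for post-treatment efficacy even if not performed with an mpMRI guided biopsy".
- **Trial Monitoring (16.4).** "Protocol deviations are to be documented using the Protocol Deviation Form".

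**The concern.** An exception to a mandatory test should name the circumstance in which that test cannot be done. Here the mandatory test is the mpMRI, but the exception names the biopsy. Two things follow: the exception covers men for whom it is not needed, and the men who do need one are left out.

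The reference to something the patient *has developed* points to a condition arising after enrolment. Men who cannot have an mpMRI or gadolinium are already excluded at entry, so only a new contraindication to the scan could matter later. That is the case one would expect this sentence to address.

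At stake is the conduct of a biopsy prompted by suspected recurrence. As written, the site must either order a scan the patient should not have, or biopsy without it and record a deviation that better wording would have avoided. Some delay while the site resolves this is possible, though nothing in the protocol shows that it would occur.

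**Working it through.** No arithmetic applies: the protocol attaches no figure to this rule and the point depends on none. The check is to apply the sentence to each combination of what the patient can and cannot undergo once a for-cause trigger has occurred.

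| Biopsy possible? | mpMRI possible? | Effect of the rule as written | Result |
| --- | --- | --- | --- |
| Yes | Yes | Scan required, then biopsy | Works |
| No | Yes | Exception applies | Nothing useful is waived: no biopsy will follow, so no scan has to precede one |
| Yes | No (new contraindication) | Exception does not apply; scan still required | Contraindicated scan, or biopsy with a deviation |
| No | No | Exception applies | Again no biopsy for the scan to precede |

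The exception operates in the second and fourth rows, where the requirement already lapses because it depends on a biopsy taking place. It does not operate in the third row, the only one where a waiver would do any work.

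The next question is whether other text covers the third row.

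1. *Exclusion criterion 3* acts at screening. It says nothing about a pacemaker, implant or contrast allergy acquired later.
2. *Appendix B* covers all imaging after FT and specifies a post-gadolinium acquisition. A new gadolinium contraindication therefore also prevents the scan as specified, even if the man can enter the scanner.
3. *The surveillance section* allows results from biopsies without mpMRI guidance to be used for efficacy. That concerns use of the result; it does not lift the requirement that a scan come before a for-cause biopsy.
4. *The additional for-cause tests* (ultrasound, CT, bone scan, PSMA/PET) are permitted, but none is named as a substitute for the mpMRI.

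None of these supplies a waiver.

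Last, what happens to the data. A biopsy done without the scan is not lost, by the surveillance section. Redo FT is not conditioned on a prior scan either: item 4 of the ablation-template principles asks only that the specified biopsy results "are positive at any point in follow-up".

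With the exception reworded to a contraindication to mpMRI, the third row becomes biopsy without scan and the other three rows are handled as they should be.

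**The case against.** The strongest reply is that the sentence is not self-contradictory. A man with a confirmed PSA rise is under evaluation. If he cannot be biopsied, the exception can be read as sparing him a pre-biopsy scan while the other for-cause tests remain open. This reading is possible but gives the exception little to do, since the requirement already depends on a biopsy. Imaging is also arguably most useful when tissue cannot be obtained. And the reading still leaves the man with an MRI contraindication without a waiver.

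A second reply is that no clinician would perform an unsafe scan, that the section is permissive about biopsy, and that the realistic worst case is one deviation form. That is fair as a statement of size. It does not defend a rule that has to be broken in order to act safely.

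A third is that the scheduled 12-month mpMRI also lacks a waiver for new contraindications, so the silence is general. This is correct, and the edit to the for-cause section would not cure it. The for-cause section differs in that it does contain an exception, and the exception names the wrong procedure.

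It also stands that reading *biopsy* as a slip for *mpMRI* is an inference about intent. The conclusion does not need it: the gap is there whatever was meant.

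**Conclusion.** The concern holds: the rule is wrong as written. Its only exception has no useful application, and a man who develops a contraindication to MRI or gadolinium after enrolment has no exemption from the scan before a for-cause biopsy.

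The importance is low. Only men with both a for-cause trigger and a new contraindication are affected, at most a very few of 57 and possibly none. The protocol gives neither rate, so no probability is claimed. There is no effect on the primary analysis, the handling of missing biopsies or the sample size. The gain from correction is a small one in patient safety and clean conduct.

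**What to change.** In For Cause Tests, reword the exception to read: *unless the patient has developed a contraindication to mpMRI (including to gadolinium contrast), in which case the for-cause biopsy may proceed without mpMRI*. Naming gadolinium settles the contrast question that Appendix B raises.

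This is a one-phrase correction at the next amendment, with no added visit, test or data field. The same amendment could state what is to be done at the 12-month visit for a man who can no longer have the scan; that is optional and separate from this point.

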# TOXICITY MANAGEMENT GUIDELINES/SAFETY MONITORING

## Falls and fractures

Monitor and manage patients at risk for fractures according to established treatment guidelines and consider use of bone-targeted agents.

## Ischemic heart disease and ischemic cerebrovascular disorders

Ischemic heart disease and ischemic cerebrovascular disorders, including events leading to death, occurred in patients treated with ADT. Monitor for signs and symptoms of ischemic heart disease and ischemic cerebrovascular disorders. Optimize management of risk factors, such as

hypertension, diabetes, or dyslipidemia. Of note, see screening exclusion criteria regarding patients with pre-existing heart disease for further clarification.

## General Concomitant Medication and Supportive Care Guidelines

The following concomitant medications and therapies are prohibited during the study. The Sponsor-Investigator must be notified in advance, or as soon as possible thereafter, of any instances in which prohibited therapies were administered. These must be reviewed for at study entry during screening.

- Any chemotherapy, anti-cancer therapy (other than study treatment[s]), or experimental therapy
- Radiotherapy to tumor lesions being assessed for tumor response prior to radiographic progression.

Subjects, who, in the assessment by the treating investigator, require the use of any of the aforementioned treatments for clinical management other than specified as allowed, should be removed from the trial. Subjects may receive other medications that the treating investigator deems to be medically necessary.

# DURATION OF TREATMENT, FOLLOW-UP & WITHDRAWALS

## Duration of Therapy

In the absence of treatment delays due to adverse event(s) (AE), treatment may continue per protocol until one of the following criteria applies:

- Disease progression
- Intercurrent illness that prevents further administration of treatment
- Unacceptable AE(s)
- Patient decides to withdraw from the study treatment
- General or specific changes in the patient's condition render the patient unacceptable for further treatment in the judgment of the treating investigator
- If a subject shows an increase in PSA (>2 ng/mL higher than baseline PSA) at 8-weeks after initiation of neoadjuvant therapy, he will be considered to have biochemical progression and will be withdrawn from the study.
- Patient non-compliance
- Termination of the study by University of Chicago PI

The reason(s) for protocol therapy discontinuation, the reason(s) for study removal, and the corresponding dates must be documented in the study EDC (REDCAP) and within study source documentation.

## Duration of Follow-Up

Subjects will be followed for survival and recurrence for up to 1-year from the date of their FT procedure. Subjects removed from study for unacceptable AE(s) will be followed until resolution or stabilization of the AE.

Refer to the study calendar (section 15) for the timing and frequency of the following activities in follow-up. Subjects in the post-op follow-up phase should be seen in clinic to collect PSA levels (per clinical SOC) and assess for survival and recurrence until death, withdrawal of consent, becoming lost to follow-up or at the end of the study (up to 1-year after FT procedure), whichever occurs first. HrQOLs (I-PSS, SHIM and the EPIC-26) will also be completed at designated follow-up visits. Subjects may also have a focused abdominal and pelvic genitourinary examination in follow-up if clinically indicated.

## Lost to follow-up

Patients who have begun but not completed active treatment with ADT who refuse to continue participation in the study, including any telephone contact, should be documented as “withdrawal of consent” rather than “lost to follow-up.”

In the absence of a clear withdrawal of consent, study teams should make every attempt to contact subjects during the post-FT follow-up phase to determine the patient’s survival or recurrence status or to collect other study data as needed following the University of Chicago Medicine Comprehensive Cancer Center (UCCCC) workflows or institution-specific requirements. A patient will be considered to be “lost to follow-up” per UCCCC workflows and policies or institution-specific requirements.

In the event that a subject has withdrawn consent to the collection of any follow-up data, the survival status of the patient can be obtained instead from publicly available death registries or other publicly available (e.g., obituaries) where it is possible to do so under applicable local laws to obtain a current survival status.

## Withdrawal of Consent

Subjects are free to withdraw from the study at any time. A subject who withdraws consent will always be asked about the reason(s) for withdrawal and the presence of any AEs. The PI and/or treating physician will continue to follow up AEs outside of the clinical study.

If a subject withdraws consent, they will be specifically asked if they are withdrawing consent to:

- All further participation in the study including any further follow up (e.g., contact for survival status, and HrQOL data collection in follow-up) and/or
- Only active treatment with ADT or the FT procedure.

The withdrawal of consent must be documented in REDCap and in source documentation.

When a subject is discontinued/withdraws to active treatment with ADT prior to completion per protocol, all applicable activities scheduled for the safety visit should be performed at the time of discontinuation. Any AEs, which are present at the time of discontinuation or withdrawal, should be followed in accordance with the safety requirements outlined in [Section 14](#_SAFETY_EVENT_AND).

# OTHER RESEARCH ACTIVITY SPECIFICATIONS

The Study Calendar summarizes the trial procedures to be performed at each visit.

## Medical History

A medical history for each subject will be obtained by the treating investigator or qualified designee. Medical history will include all active conditions, and any condition diagnosed within the prior 10-years that are considered to be clinically significant by the treating investigator. Details regarding the disease for which the subject has enrolled in this study will be recorded separately as part of a subject’s demographics and not listed as medical history.

Medical history must be graded per the National Cancer Institute’s Common Terminology Criteria for Adverse Events (CTCAE) v.5 to facilitate the identification of grade changes from baseline. Subjects will be asked about their medical conditions at each study visit (e.g., any new admissions or changes in existing conditions) and new medical history, if any, will be recorded throughout the study.

## Prior and Concomitant Medications

Prior Medications

The treating investigator or qualified designee will review prior medication use, including any protocol-specified washout requirements, and record prior medication taken by the subject within 28-days before starting the trial (time of consent). Treatment for the disease for which the subject has enrolled in this study will be recorded separately and not listed as a prior medication.

Concomitant Medications

The treating investigator or qualified designee will record all medications (including any supplements), if any, taken by the subject during the trial as specified in the Study Calendar (section 15) including those taken for any AEs.

